## Abstract

**Background:**

Type 2 diabetes (T2D) is associated with increased risk of morbidity and premature mortality. Among those at high risk, incidence can be halved through healthy changes in behaviour. Information about genetic and phenotypic risk of T2D is now widely available. Whether such information motivates behaviour change is unknown. We aim to assess the effects of communicating genetic and phenotypic risk of T2D on risk-reducing health behaviours, anxiety, and other cognitive and emotional theory-based antecedents of behaviour change.

**Methods:**

In a parallel group, open randomised controlled trial, approximately 580 adults born between 1950 and 1975 will be recruited from the on-going population-based, observational Fenland Study (Cambridgeshire, UK). Eligible participants will have undergone clinical, anthropometric, and psychosocial measurements, been genotyped for 23 single-nucleotide polymorphisms associated with T2D, and worn a combined heart rate monitor and accelerometer (Actiheart®) continuously for six days and nights to assess physical activity. Participants are randomised to receive either standard lifestyle advice alone (control group), or in combination with a genetic or a phenotypic risk estimate for T2D (intervention groups). The primary outcome is objectively measured physical activity. Secondary outcomes include self-reported diet, self-reported weight, intention to be physically active and to engage in a healthy diet, anxiety, diabetes-related worry, self-rated health, and other cognitive and emotional outcomes. Follow-up occurs eight weeks post-intervention. Values at follow-up, adjusted for baseline, will be compared between randomised groups.

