### Immediate post-intervention assessment

Following allocation to a trial group, participants are mailed an intervention instruction letter, standard lifestyle advice along with the relevant intervention materials, and an immediate post-intervention questionnaire. The instruction letter asks participants to read through the intervention materials until they feel happy that they understand them, complete the immediate post-intervention questionnaire, and return it in the enclosed freepost reply envelope. A reminder letter, along with a second copy of the questionnaire, is sent if the first is not returned within two weeks. If the questionnaire is still not returned after four weeks, a second reminder letter is sent.

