Diabetes-related worry*	Assessed using the Cancer Worry Scale (CWS) [82]. The CWS consists of 6 items that assess the frequency of worries about developing cancer and the effect that these worries have on mood and daily functioning. These items have been adapted for use in the context of T2D and have been shown to have acceptable test-retest reliability and good internal consistency [83].		✓		✓
Anxiety*	Assessed using the short-form of the state scale of the Spielberger State Trait Anxiety Inventory (STAI) [84]. The short-form STAI consists of 6 items that comprise the most highly correlated anxiety-present and anxiety-absent items from the full-form of the STAI. Scores obtained using this short-form have been shown to be highly correlated with scores obtained using the full-form of the STAI [84].		✓	✓	✓
Intentions to be physically active and engage in a healthy diet*	Assessed using 4 items. Each item includes a statement (e.g., “I intend to be more physically active in the next 8 weeks.”) evaluated on a 5-point response scale, ranging from “extremely unlikely” to “extremely likely”. These items have been adapted according to recommendations provided by Ajzen [77] and have been used in previous research [78,85].		✓	✓	✓
Self-reported weight*	Participants are asked what their current weight is, without shoes, in either stones or kilograms. Detailed descriptions of the reliability and validity of self-reported weight have been published elsewhere [86].		✓		✓
Self-reported diet*	Assessed using the Food Frequency Questionnaire (FFQ) [87]. The FFQ contains a list of 130 foods, including 12 fruit items and 26 vegetable items. Only the fruit and vegetable items are assessed at follow-up. Detailed descriptions of the reliability and validity of the FFQ have been published elsewhere [87,88].	✓			✓

*Secondary outcomes.

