### Statistical analysis

We will use univariate descriptive statistics (means, standard deviations, numbers, and percentages) to summarise the characteristics of the study sample at baseline. All trial analyses will be performed on an intention-to-treat basis (i.e., analysis of data according to randomised study group, regardless of whether or not the intervention was received). Those with missing outcome data will be excluded from the analyses (a complete case approach). If necessary, a sensitivity analysis will be performed to investigate the effect of having excluded participants with missing data for the primary outcome only. We will use a multiple imputation procedure with a ‘missing at random’ assumption to impute missing outcome data [89]. Participants with missing baseline data will be included in the analyses using the missing-indicator method [90].

An analysis of covariance (ANCOVA) regression model will be used to determine if differences exist in mean PAEE at follow-up, adjusted for baseline, between randomised groups. Exploratory analyses will be conducted to examine potential moderators and mediators of the intervention effects on PAEE (i.e., sex, age, body mass index, time since the Fenland Study, and baseline measurements of the trial outcomes). A further subgroup analysis will explore whether a high or low risk estimate moderates the effect of type of T2D risk estimate (i.e., genetic or phenotypic) on PAEE. Similar regression analyses will be used to examine differences in all secondary outcomes. Acceptability will be assessed by summarising recruitment rates, loss to follow-up, and reasons for loss to follow-up. Additionally, differences in responses to questions regarding the perceived accuracy of the risk estimates, as well as the retention and discussion of the risk estimates will be examined.

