## Discussion

To enhance our understanding of the effects of communicating information about genetic and phenotypic risk of T2D on risk-reducing health behaviours, larger and higher quality randomised controlled trials are needed [39]. Such trials will have the power to detect small, but still clinically important, effect sizes while allowing for a more comprehensive analysis of potential mediators and moderators of effects of risk communication. Studies should include precise measures of behaviours and behavioural intentions, a comprehensive assessment of individual risk perception, and a sound theoretical framework so as to further elucidate the motivational impact of risk communication. Each of these recommendations is consistent with the MRC Framework for the development and evaluation of complex interventions to improve health [93], and highlight the strengths of this study.

Previous research has demonstrated that healthy changes in behaviour can significantly reduce the incidence of T2D, even among those at high risk [2]. However, translation of these findings into preventive strategies has proven difficult, as it requires that individuals are motivated to adopt and maintain the behavioural changes necessary to prevent T2D [94]. The DRCT will provide robust evidence of the potential for beneficial or harmful effects of communicating genetic and phenotypic risk information on risk-reducing health behaviours and the potential role of such information in T2D preventive strategies.

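### The eight-week anxiety comparison is complete-case with no planned missing-data check, although a post-intervention anxiety score that could inform it is already collected

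*Protocol article*

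**What the plan says.** Table 1 of the protocol article marks anxiety as a secondary outcome: "Assessed using the short-form of the state scale of the Spielberger State Trait Anxiety Inventory (STAI"). It is ticked at trial baseline, immediately post-intervention and at follow-up. For the middle assessment, participants read the materials sent to them and then "complete the immediate post-intervention questionnaire, and return it in the enclosed freepost reply envelope". It is thus the score closest to the moment the risk estimate is received.

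The abstract says "Follow-up occurs eight weeks post-intervention" and then "Values at follow-up, adjusted for baseline, will be compared between randomised groups". Statistical analysis describes an ANCOVA of PAEE at follow-up adjusted for baseline. It says that similar regressions will be used for every secondary outcome, without naming a time point for them.

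On missing outcomes the section is explicit: "Those with missing outcome data will be excluded from the analyses (a complete case approach"). A sensitivity analysis is planned only if judged necessary, and its purpose is to "investigate the effect of having excluded participants with missing data for the primary outcome only"; it uses multiple imputation under missing at random. Loss to follow-up and its reasons will be summarised. Sample size allows for 20% attrition.

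**The concern.** For anxiety the trial holds a score taken after randomisation and before most follow-up loss can occur. The complete-case rule, applied to an ANCOVA with baseline as the only covariate, makes no use of that score at eight weeks. A participant who reported high anxiety on reading the estimate and did not respond at eight weeks contributes nothing to the eight-week comparison, and no planned analysis asks whether this matters.

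Baseline adjustment deals with dropout that depends on baseline anxiety. It does not deal with dropout that depends on the reaction to the estimate. If that dependence is stronger in the arms receiving an estimate than in controls, the responders in those arms are selectively calm, and the comparison leans towards finding no harm from risk communication. A missing-data check matters most for a harm-type outcome, and here the check is restricted to PAEE.

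**Working it through.** **The plan's own figure.** Residual SD of PAEE = 15.4 × √(1 − 0.69²) = 11.15 kJ/kg/day. Per group, n = 2 × (2.393 + 0.842)² × 11.15² / 4.1² ≈ 155, at two-sided 1.67% and 80% power. Three groups give 465 completers, and 465 / 0.80 = 581.25, rounded up to 582. The stated 465 and about 580 are reproduced. They concern PAEE and are unaffected by this point.

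**How many are at stake.** 580 × 0.20 = 116 participants, about 39 per arm, would be absent from an eight-week comparison. How many of them would have returned a post-intervention score is not given.

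**Inputs for the illustration.**
- From the protocol: 20% attrition per arm and 155 completers per arm.
- Assumed, not in the document: anxiety SD 1; correlations baseline–post 0.5, baseline–follow-up 0.5, post–follow-up 0.6; a true group difference of 0.3 SD post-intervention and 0.2 SD at eight weeks; everyone returns the post-intervention score; the log-odds of later dropout rise by 0.5, 0.8 or 1.2 per SD of post-intervention anxiety in the intervention arm and by 0 in controls.

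**Results of a large-sample simulation (true eight-week difference 0.20 SD).**

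| Slope, intervention / control | Complete-case ANCOVA | Likelihood model also using the post-intervention score |
|---|---|---|
| 0.5 / 0 | 0.167 | 0.20 |
| 0.8 / 0 | 0.147 | 0.20 |
| 1.2 / 0 | 0.130 | 0.20 |
| 0.8 / 0.8 | 0.20 | 0.20 |
| 0 / 0 | 0.20 | 0.20 |

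Repeat runs of the complete-case figures vary by up to 0.003. The shortfalls are 0.033, 0.053 and 0.070 SD, or about 17%, 27% and 35% of the true effect.

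**Check by hand.** Suppose selective dropout lowers the mean post-intervention score of the retained intervention arm by s. Mean follow-up anxiety among those retained falls by 0.6s and mean baseline by 0.5s. ANCOVA with a slope of about 0.5 removes 0.5 × 0.5s = 0.25s. The remaining bias is about 0.6s − 0.25s = 0.35s. The simulated shortfalls correspond to s = 0.033/0.35 = 0.09 up to 0.070/0.35 = 0.20 SD.

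For scale, losing the most anxious 2%, 5% or 10% of an arm, with normal scores, lowers its mean by 0.05, 0.11 or 0.20 SD. Carried through at 0.35, that is a bias of about 0.02, 0.04 or 0.07 SD.

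**Against precision.** With 155 per arm, the standard error of the baseline-adjusted difference is √(2 × (1 − 0.5²) / 155) = 0.098 SD. Every bias shown is smaller than one standard error.

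**The case against.** Three objections deserve weight.

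First, a reader might infer that the plan tests anxiety only at eight weeks, so that a short-lived reaction goes untested and the post-intervention score is thrown away. The document does not support this. The sentence with "Values at follow-up, adjusted for baseline, will be compared between randomised groups" is a one-line abstract summary, and Statistical analysis gives no time point for secondary outcomes. Table 1 lists starred outcomes (diabetes risk representations; self-efficacy, response efficacy and perceived severity) measured at baseline and post-intervention but not at follow-up. Analysing all secondary outcomes therefore requires some post-intervention comparisons. Nothing excludes one for anxiety, and the choice of time point per outcome may be in an analysis plan that is not shown. Someone who answers post-intervention and then drops out would be a complete case for such a comparison. This objection stands in full.

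Second, a reader might hold the trial to the Discussion's statement that "The DRCT will provide robust evidence of the potential for beneficial or harmful effects of communicating genetic and phenotypic risk information". That sentence goes on to specify risk-reducing health behaviours, so it makes no promise about anxiety. This also stands.

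Third, anxiety-driven dropout that differs between arms is a hypothesis. The effects, correlations and slopes are assumed, the steepest slope is an odds ratio of e^1.2 = 3.3 per SD, and the bias is below one standard error. That limits how much weight the point can bear. It does not remove it: the complete-case rule and the restriction of the sensitivity analysis to the primary outcome are stated rules, not omissions. Summarising reasons for loss describes dropout without correcting an estimate.

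The same rules apply to every secondary outcome. Anxiety is singled out because it has both a post-intervention and an eight-week score and bears on harm.

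**Conclusion.** The point holds as a cheap improvement, not as an error that undermines the trial. As written, an eight-week anxiety comparison adjusted for baseline omits participants with a post-intervention score and no follow-up score, and no missing-data check is planned for it.

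The consequence depends on dropout. If it rises with post-intervention anxiety more in a risk-estimate arm than in controls, the comparison is biased towards no harm: 0.13 to 0.17 SD against a true 0.20 SD in the scenarios above. If the dependence is equal or absent there is no bias, and if it were stronger in controls the bias would run the other way. The document gives no information on which applies. The conclusion does not extend to acute anxiety being untested, and it leaves the primary analysis and the sample size unchanged.

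**What to change.** In Statistical analysis, add for anxiety: the STAI score will be analysed in one repeated-measures model, with the post-intervention and follow-up scores as outcomes and with group, time, group-by-time, baseline score and baseline-by-time as terms. It will include every participant with at least one post-randomisation score, and group differences will be reported at both times.

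This also settles the anxiety time points, which the article leaves open. It needs a short addition to the text and one model on data already collected, with no new questionnaire, contact or participant.

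The costs are one more reported anxiety contrast for each pair of groups, and reliance on the assumption that dropout is explained by the observed anxiety scores. The model does not help with participants who return neither post-randomisation questionnaire.

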**Discussion:**

This study will provide much needed evidence on the effects of providing information about the genetic and phenotypic risk of T2D. Importantly, it will be among the first to examine the impact of genetic risk information using a randomised controlled trial design, a population-based sample, and an objectively measured behavioural outcome. Results of this trial, along with recent evidence syntheses of similar studies, should inform policy concerning the availability and use of genetic risk information.

**Trial registration:**

Current Controlled Trials ISRCTN09650496

## Background

Type 2 diabetes (T2D) is associated with costly complications including cardiovascular disease, neuropathy, and blindness, as well as premature mortality [1]. Previous research has demonstrated that the development of T2D can be prevented through healthy changes in behaviour, even among those at high risk [2]. More specifically, several randomised controlled trials including individuals with impaired glucose tolerance, have reported reductions in risk by as much as 40% to 60% following interventions to promote moderate weight loss through a combination of changes in physical activity and diet [3].

There are many well-established risk factors for T2D, including demographic (age and sex), metabolic (obesity), and behavioural factors (physical inactivity and poor diet) [1]. Evidence from twin and family history studies has shown that genetic factors also play an important role in determining individual susceptibility [4]. While it has been estimated that between 30% and 70% of T2D risk can be attributed to genetic factors, until recently, the number of genes involved and the extent to which each contributes to the development of the disease remained largely unknown [4,5]. However, with the implementation of large-scale studies of genetic association, our understanding has greatly increased [4,5]. To date, more than 40 single nucleotide polymorphisms (SNPs) associated with increased risk of T2D have been identified [6-12].

Along with the discovery that several genetic loci are associated with T2D came an expectation that this information would lead to improved prediction of disease risk [13-16]. Multiple risk models that incorporate routinely collected data (e.g., sex, age, body mass index, parental history of T2D, drug treatment, and smoking status) have already been shown to predict the risk of developing T2D reasonably well [17,18]. However, contrary to expectations, there currently appears to be little additional predictive benefit from incorporating genetic information into non-genetic risk models [17-19]. A recent meta-analysis of published data on T2D risk prediction showed that the predictive value of SNPs associated with T2D was significantly poorer than the predictive value of non-genetic risk models, with the area under the receiver operating characteristic curve ranging from 0.59 to 0.60 and from 0.78 to 0.89, respectively [19]. Furthermore, when genetic information was incorporated into non-genetic risk models, no clinically significant improvements in the models’ predictive values were observed. In spite of these findings, direct-to-consumer genetic tests that claim to predict susceptibility for T2D are now widely available [20], and some researchers are optimistic that this information might enhance preventive strategies [13,21,22].

Consistent with health behaviour theory, it has been suggested that informing individuals of their genetic risk of T2D may motivate engagement in risk-reducing health behaviours (i.e., increased physical activity and a healthy diet) [23,24]. It is thought that genetic risk information could be perceived as more personally relevant than risk information based on other markers of disease. Individuals who are informed that they are at increased risk based on their genotype may consequently have greater motivation to change their behaviour than those informed of increased risk based upon another less salient method (e.g., phenotypic characteristics), or those informed of a low risk. In contrast, it has also been suggested that informing individuals of their genetic risk of T2D might de-motivate some to change their behaviour [24,25]. They could perceive their risk as being uncontrollable due to its genetic determinants, which are often thought to be immutable [26]. Those informed of a high risk as determined by their genotype might consequently adopt a sense of fatalism, and those informed of a low risk might be falsely reassured. In both instances, such attitudes would likely result in a lack of motivation to change behaviour.

In order to take full advantage of the motivational impact of genetic risk information, a deeper understanding of the mechanisms through which it may motivate behaviour change is necessary [23]. Several health behaviour theories, including the Protection Motivation Theory (PMT), indicate that engagement in risk-reducing health behaviours is largely influenced by an individual’s pre-existing perception of risk [27,28]. Although there has been much research on the role of perceived risk as a determinant of behaviour, how individuals construct their perception of risk and the extent to which it directly influences behaviour remains unclear [28-30]. The most common method used for assessing perceived risk is through self-report of absolute risk, which is often numerically based [31]. Studies have shown, however, that individuals experience difficulty understanding risk estimates based on numerical presentations of probability or relative risk [32]. Although this may be due in part to problems of numeracy [33,34], some research suggests that it is because individuals construct their perception of risk in ways that are not entirely rational [30,32,35]. The Common Sense Model of self-regulation of health and illness (CSM) provides a framework for understanding how perceived risk is constructed [36]. Previous research highlights the importance of using the CSM as the conceptual basis for identifying the content and influences of perceived risk [32], and also supports examining the utility of the PMT to predict changes in behaviour [37,38]. Together, the CSM and the PMT could elucidate which components of T2D risk information effectively motivate change in risk-reducing health behaviours.

To date, no research has examined the effect of communicating genetic risk of T2D on the risk-reducing health behaviours of physical activity and diet. The majority of genetic risk communication research has focused on diseases that have single-allele associations and do not have complex gene-lifestyle interactions [39,40]. A recent systematic review by Marteau et al. [39], identified seven randomised controlled trials and six analogue studies that evaluated the effects of providing genetic risk information for a range of diseases (e.g., lung cancer, heart disease, and Alzheimer’s disease). The studies explored a variety of behavioural outcomes (e.g., smoking cessation, medication adherence, and vitamin use), many of which were assessed through imprecise self-report measures. Only two of the trials included in the review assessed self-reported changes in physical activity and diet, and neither was in the context of T2D. In line with the findings of similar reviews [41-44], the authors concluded that the limited number of low quality studies precluded strong statements regarding the effect of communicating genetic risk information on non-clinical risk-reducing behaviours. There was no evidence that genetic risk information de-motivated individuals. However, it does appear that genetic risk information may not greatly motivate behaviour change, but may have a small effect on intentions to change behaviour [39]. Given the rapid growth in our understanding of the genetic basis of complex disease and the increasingly widespread availability of genetic tests, there is a pressing need to improve our knowledge of the potential for beneficial or harmful effects of informing people of their genetic risk of disease [45,46].

